### Setting and participants

To align with the typical motor development phase associated with CMS, recruitment of participants will be targeted at children 8–12 years, spread across 4 school years/grades. As this age range straddles two levels of schooling (primary/elementary, secondary/middle) 6 schools from each level at each site will be invited to the trial. Existing university networks will be used to recruit schools and if more than the required number of schools replies positively, schools will be stratified into age groupings prior to random selection (coin toss) of inclusion into the study. Recruitment will result in 3 sites each containing 12 schools (6 experiment, 6 control) evenly distributed across primary/elementary, secondary/middle schools yielding approximately 300 students at each site and a total of ~904 students for the trial. Representatives of each school will be invited to an information event to support their decision-making in becoming involved.

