### Sample size calculation

A sample size calculation was completed to estimate the number of schools needed for the trial. Sampling for a two-group clustered RCT is developed around data from previous clustered trials assessing game skill (e.g., support, decision-making and defence) and fundamental movement skill (e.g., throw, kick, under-arm throw and catch) development [23, 24]. The lowest effects in these trails were observed for the fundamental movement skill of catch (effect *d* = 0.4), and the game skill of decision making (*d* = 0.4).

Without accounting for clustering among schools (schools being alike and reducing the power of data), approximately 156 students are required to detect an effect of d = 0.4 at 80% power with alpha 0.05. To adjust for clustering, the following correction factor is applied (1+ (m– 1) x ICC) [25], where m = students per school and ICC = the intra-class correlation coefficient (between school variance / between school variance + within school variance). Assumptions are based on clustering at the school level (one class recruited per school, with ~25 students per class), and a conservative ICC of 0.20 based on data from a school based intervention [22], resulting in a correction factor of 5.8. The resulting student sample is ~904 students at 36 schools (18 intervention, 18 control).

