### Consent and permissions

Prior to the intervention, parents/carers of the participating students and the Headteacher/Principal of the school, acting as a gatekeeper, will be provided with study information and provide written informed consent. The students will also be provided with an information sheet and assent form, specifically written to respond to their reading age. If the Headteacher agrees to students at their school participating in the intervention, they will need to sign and return the gatekeeper consent form to the research team and distribute information packs to prospective participating students and their parents/carers. If parents/carers permit their child to participate in the intervention they will need to complete, sign, and return the informed consent forms to school teachers along with assent forms from the children. All completed forms will then be collected by the research team from teachers.

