### Intervention

MOGBA is presented as a series of 14 resource cards with the front of the card illustrating the game as well as sections describing ’what you need’ (equipment), ’set up like this’, ’keep it safe’ and ’change the game’. On the reverse of the card, there is an assessment framework that illustrates the movement being assessed and provides criteria for the practitioner to use to score the child’s performance using two constructs. The assessment has two focal aspects most closely related to the movement being assessed (i.e. two aspecsts from: head, arms, legs or body) with associated criteria, alongside which the numerical values are placed following a child’s assessment. Given the complex nature of the assessment and projected groups size (20–25 children), a subset of children will be selected for assessment during each activity.

The resource also contains an ’introductory section’ that explains the nature of children’s movement development and the purpose of MOGBA, as well as a ’change the challenge’ section. ’Change the challenge’ provides guidance for practitioners on how to differentiate the activity to meet the diverse needs of children in relation to Goodway, Osmun & Gallahue’s [1] notion of Space, Effort and Relationships.

Facilitators recruited by each site will deliver the 14 MOGBA activities in schools over a 9-week period, following two three-hour facilitator development workshops. Facilitators are affiliated to the University and have considerable experience in Physical Education and/or coaching settings. At each site, all 14 MOGBA activities, ranging in categories (Stability (S), Object Control (OC) and Locomotion (L)) and complexity of movement (across three phases) will be delivered, with two sessions each week lasting between 45–60 minutes per session. One MOGBA activity, as presented on the front of the activity resource card and use of the associated assessment protocol will last the duration of the session. An extra four sessions have been accounted for within the intervention period to cater for typical disruptions to timetables. Fig 1 provides an example of the ‘Play it’ side of a MOGBA activity resource card.

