### Statistical analyses

This trial aims to examine whether MOGBA (a) improves children’s movement competence (Dragon Challenge); (b) increases MVPA during PE lessons (acceleromters), (c) reduces sedentary time both in school and outside of school (accelerometers) (d), improves physical fitness (plank and standing long jump), (e) improves self-perceptions of game and physical competence (Game Play Perception Profile). We hypothesize that children in the MOGBA intervention, compared to those in the control group, will display more favorable changes in these variables identified above.

Statistical analyses of the primary and secondary outcomes will be conducted with linear mixed models using IBM PASW Statistics 25 (SPSS Inc. Chicago, IL) software. Impacts are estimated using an intention-to-treat (ITT) approach, with alpha levels set at p < 0.05. Linear mixed models will be fitted to compare continuous outcomes. Group, time, and group-by-time interaction will be assessed as fixed effects within the model, with covariates of gender and year level also included as fixed effects. The school a student belongs to and the research site will be included as a random intercepts within the model to account for the multi-level nature of the data, and subject (student ID) will be included as a random intercept to model repeated measures at the individual level. Differences of means and 95% confidence intervals (CIs) will be determined using the linear mixed models. If the variables used for secondary outcomes (questionnaires) fail tests of multivariate normality, non-parametric methods will be utilised, or the variables for use in the linear models will be an individual’s factor score from a confirmatory factor analysis of the scales with the appropriate estimator chosen given the non/normal nature of the data.

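### The ~904 children the calculation needs analysed is also given as the number recruited, with no margin for class size, consent or loss; the shortfall in children could be large, the resulting loss of power is small

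*Protocol article*

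**What the plan says.** All references are to the Protocol article.

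- **Sample size calculation.** Before clustering, "approximately 156 students are required to detect an effect of d = 0.4 at 80% power with alpha 0.05". The correction factor uses about 25 children per school (one class) and an ICC of 0.20, giving 5.8. The section concludes: "The resulting student sample is ~904 students at 36 schools (18 intervention, 18 control".
- **Setting and participants.** Three sites of 12 schools each are expected to give the same total: "yielding approximately 300 students at each site and a total of ~904 students for the trial".
- **Intervention.** Sessions are planned for a "projected groups size (20–25 children").
- **Consent and permissions.** Participation is opt-in. Parents or carers must complete, sign and "return the informed consent forms to school teachers along with assent forms from the children". No uptake rate is given.
- **Trial design.** The primary outcome is measured again at a 3-month post-test. No loss rate is given.
- **Statistical analyses.** Tests are run "with alpha levels set at p < 0.05", with 95% confidence intervals. Neither this section nor the sample size section says whether the test is one-sided or two-sided.

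**The concern.** The formula in the sample size section gives the number of children whose outcomes must be available for analysis. The recruitment section uses that same number as what recruitment will yield. The two can be equal only if nobody is lost between joining and the post-test.

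The class size adds to this. The calculation takes about 25 per class, which is the top of the group size given under Intervention, and a full class is the ceiling on enrolment when each child needs a returned parental form and an assent form.

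At stake is mainly the credibility of the stated size. A trial that recruits its 36 schools exactly as planned could still report far fewer than 904 analysed children, and a reader would take this for a recruitment failure when it was built into the plan. The stated 80% power is also affected, but much less.

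**Working it through.** **Inputs from the article.** d = 0.4; power 80%; alpha 0.05, sidedness not stated; unclustered total 156; m ≈ 25 per school; ICC 0.20; 36 schools, 18 per arm; group size 20–25.

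**1. Reproduce the stated figures.**
- Unclustered total = 4 × ((z for alpha + z for power)/d)².
- One-sided 0.05: 4 × ((1.645 + 0.842)/0.4)² = 154.6, or 78 per arm and 156 in total. This matches.
- Two-sided 0.05: 4 × ((1.960 + 0.842)/0.4)² = 196.2, or 99 per arm and 198 in total. This does not match.
- Correction factor: 1 + (25 − 1) × 0.20 = 5.8.
- 156 × 5.8 = 904.8, reported as ~904, and 904.8/25 = 36.2 schools, reported as 36.

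The arithmetic reproduces. Because ~904 is just 156 × 5.8, it contains no hidden allowance for refusal or loss.

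**2. Children in 36 single classes.** 36 × 20 = 720 and 36 × 25 = 900. The stated total needs 904/36 = 25.1 per school.

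**3. Power when fewer children per school are analysed.** Effective number = 36m/(1 + 0.2(m − 1)). Power = Φ(0.4 × √(effective number/4) − z), with z = 1.645 (one-sided) or 1.960 (two-sided).

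| Analysed per school | Children | Effective number | Power, one-sided 0.05 | Power, two-sided 0.05 |
|---|---|---|---|---|
| 25 | 900 | 155.2 | 80.1% | 70.2% |
| 20 | 720 | 150.0 | 78.9% | 68.8% |
| 15 | 540 | 142.1 | 77.0% | 66.4% |
| 12 | 432 | 135.0 | 75.1% | 64.2% |

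From 25 to 15 per school the trial loses 40% of its children but only about 3 to 4 points of power.

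**4. Whole schools lost, at 15 analysed per school.** This scenario is assumed. With 33 schools the effective number is 33 × 15/3.8 = 130.3, and power is 73.8% one-sided or 62.7% two-sided. With 32 schools it is 32 × 15/3.8 = 126.3, and power is 72.7% or 61.3%.

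**5. Illustration of the shortfall in children.** The article gives no consent or retention rate, so these are assumptions.
- 80% consent and 90% retention: 720 × 0.72 = 518 to 900 × 0.72 = 648 analysed, which is 28–43% below 904. Power is 76.7–78.3% one-sided or 66.0–68.0% two-sided.
- 75% consent and 90% retention: 720 × 0.675 = 486 to 900 × 0.675 = 608 analysed, which is 33–46% below 904.

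All power figures use the plan's own unadjusted comparison of two groups and a normal approximation.

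**The case against.** **The figures are approximate and agree at 25 per class.** This stands. 36 × 25 = 900 is within 0.5% of a total written with a tilde, and it gives 80.1% power on the plan's basis. A reader who solves the formula for an effective number of exactly 156 would get 26 per school, above the plan's own range, and might infer that the stated figures cannot be reached even with full classes. The documents do not support that. The 156 is itself rounded up from 154.6, and with the unrounded value 24.3 per school is enough.

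**The 20–25 is a session size, not a recruitment forecast.** This is fair in part. It is given to explain why only some children are assessed in each activity, and 25 lies inside it. But it is the only range for group size that the trial's methods give, and the calculation uses its upper end.

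**Recruitment could mean children who have already consented.** The wording permits this. Even so, 36 classes of at most 25 cannot supply 904 consented children unless nearly all consent, and loss by the post-test remains uncovered.

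**The large shortfall rests on outside rates.** Correct. Without assumed rates the documents support only 720–900 before consent and loss.

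**Power hardly moves, and the planned mixed model may help.** Both stand. The repeated-measures model can use baseline data and keep children seen once, which could raise power above the table. It does not restore the stated number of children.

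**Other problems matter more.** Also true. Sidedness takes power at 25 per school from 80% to about 70%, more than class size does. The Abstract's layout (eight schools per site with two classes each, so 24 schools) conflicts with the 36 schools used here and needs its own reconciliation.

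**Conclusion.** The point holds as one of an unsupported stated size, not of wrong arithmetic. The number required for analysis is also presented as the number recruited, and under the 36-school, one-class layout it is approached only with classes of about 25, full consent and full retention.

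The documents alone put the ceiling at 720–900 children. A shortfall of a quarter to almost a half below 904 is illustrative only, since it depends on assumed consent and retention.

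The power consequence is modest: about 1 point at 20 analysed per school and 3 at 15 on the one-sided convention, more if whole schools withdraw. A reader might infer that small classes or dropout are what puts 80% power out of reach. They are not the main reason. If the test is two-sided, 36 schools give about 70% even at 25 per school, and at most 76.5% however large the classes. The figures assume d = 0.4, ICC 0.20 and no gain from baseline adjustment.

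**What to change.** No additional enrolment is proposed. In the article:

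1. Use one class size in Sample size calculation, Setting and participants, and Intervention.
2. State expected consent and retention as assumptions, each with a range.
3. Replace ~904 with 36 × the expected analysed number per school (class size × consent × retention), and show recruited and analysed numbers separately.
4. Restate power for the analysed number and say whether alpha is one-sided or two-sided. At 15 analysed per school, for example, it is 77% one-sided or 66% two-sided.
5. Add one scenario with a few schools lost, such as 33 or 32 schools.

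The cost is rewording and a short recalculation. The stated size and power become less favourable, but they will match what the design can deliver.

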### Consent and permissions

Prior to the intervention, parents/carers of the participating students and the Headteacher/Principal of the school, acting as a gatekeeper, will be provided with study information and provide written informed consent. The students will also be provided with an information sheet and assent form, specifically written to respond to their reading age. If the Headteacher agrees to students at their school participating in the intervention, they will need to sign and return the gatekeeper consent form to the research team and distribute information packs to prospective participating students and their parents/carers. If parents/carers permit their child to participate in the intervention they will need to complete, sign, and return the informed consent forms to school teachers along with assent forms from the children. All completed forms will then be collected by the research team from teachers.

### Randomization

Following baseline assessments, schools at each site will be ranked by their local socio-economic identifier within schooling level strata (primary/elementary, secondary/middle schools). An individual not involved in the research project will then randomize schools within ranked pairs to either the MOGBA intervention or a wait list control group using a random number generator.

### Intervention

MOGBA is presented as a series of 14 resource cards with the front of the card illustrating the game as well as sections describing ’what you need’ (equipment), ’set up like this’, ’keep it safe’ and ’change the game’. On the reverse of the card, there is an assessment framework that illustrates the movement being assessed and provides criteria for the practitioner to use to score the child’s performance using two constructs. The assessment has two focal aspects most closely related to the movement being assessed (i.e. two aspecsts from: head, arms, legs or body) with associated criteria, alongside which the numerical values are placed following a child’s assessment. Given the complex nature of the assessment and projected groups size (20–25 children), a subset of children will be selected for assessment during each activity.

The resource also contains an ’introductory section’ that explains the nature of children’s movement development and the purpose of MOGBA, as well as a ’change the challenge’ section. ’Change the challenge’ provides guidance for practitioners on how to differentiate the activity to meet the diverse needs of children in relation to Goodway, Osmun & Gallahue’s [1] notion of Space, Effort and Relationships.

Facilitators recruited by each site will deliver the 14 MOGBA activities in schools over a 9-week period, following two three-hour facilitator development workshops. Facilitators are affiliated to the University and have considerable experience in Physical Education and/or coaching settings. At each site, all 14 MOGBA activities, ranging in categories (Stability (S), Object Control (OC) and Locomotion (L)) and complexity of movement (across three phases) will be delivered, with two sessions each week lasting between 45–60 minutes per session. One MOGBA activity, as presented on the front of the activity resource card and use of the associated assessment protocol will last the duration of the session. An extra four sessions have been accounted for within the intervention period to cater for typical disruptions to timetables. Fig 1 provides an example of the ‘Play it’ side of a MOGBA activity resource card.

**Fig 1 pone.0253747.g001:**
[figure not shown]
Example of a MOGBA activity (Space Invaders 4, Phase 3, Object Control) front of card ‘Play it’.

On the reverse of the card, there is an assessment rubric based on various movement frameworks [1, 26], as demonstrated in Fig 2 below. This assessment rubric relies on developmental perspectives of movement competence by establishing the observed child’s performance in relation to the movement task, using assessment criteria. Three phases of movement competence have been criterion referenced ((1) emerging, (2) can do, (3) accomplished), in a similar way to other movement assessment protocols that have been well received in feasibility trials within similar settings to the intended use of MOGBA [27]. To increase the sensitivity of assessment and negate a potential ceiling effect in scoring the movement task, a further two components of movement competence have been identified for assessment; namely, (1) confidence and (2) proficient. These assessment components have been introduced to encapsulate the broader contextual demands of movement competence and recognize the child’s ability to perform the movement tasks with greater degrees of freedom [28, 29].

**Fig 2 pone.0253747.g002:**
[figure not shown]
Example of a MOGBA activity (Space Invaders 4, Phase 3, Object Control) reverse of card ‘Assess it’.

The MOGBA activities are arranged by Phase (1, 2 and 3) and category of movement (Stability (S), Object control (OC) and Locomotion (L)): Phase 1: ’Space Invaders 1 (2v1)’ (OC), ’T-Time’ (S), ’Square Ball’ (OC) and ’Raid’ (L). Phase 2: ’Space Invaders 2 (3v2) (OC), ’Cornerball’ (OC), ’End Zone 1’ (S), Kabbadi (S), ’Gateways’ (L) and ’Potted Skills Circuit’ (L). Phase 3: ’Space Invaders 3 (3v4)’ (OC), ’Mat Rounders’ (OC), ’End zone 2’ (S) and ’Tag’ (L).

MOGBA activities are designed as innovative, dynamic and fun activities that are non-sport specific and presented as three distinct phases. Phase 1 activities involve simple movement tasks, often performed at individual level and without the complexity associated with the utilization of perceptual-cognitive skills such as anticipation and decision making [30] needed in partner, small group work or team games. This phase is seen as an opportunity for children to use previously acquired FMS in more complex situations, but in a way that supports the transition of a child’s movement development from FMS to CMS in a progressive and staged way.

Phase 2 activities build upon the re-introduction of FMS in more complex activities experienced in Phase 1 to further explore the child’s ability to refine, adapt, combine and apply FMS in more pressurized environments. There is a continuous theme of space exploration throughout the phases, within the ‘Space Invaders’ activities that allows children to experience the significance of space in game play in a range of increasingly complex situations.

Phase 3 activities are situated as close to traditional forms of game play as possible, without the constraints of rules and codes associated with a specific game. In phase 3, children are asked to apply learning from Phase 1 and 2 to respond to the demands of the activity and use assessment feedback to improve their performance of movement tasks within the games. This progressive nature of activity development is appropriate given observations of players coupling their actions in both space and time to information unfolding from key environmental and task constraints during performance [31].

Whilst most of the sections within the ‘play it’ resources are self-explanatory, the ‘Change the game’ section challenges the practitioner to modify the game to challenge children in different ways. This is based on theories of differentiation that suggests modifying core aspects of activity design will enable children to engage in differing ways that better meet their needs [32].

To further differentiate opportunities for participating children, a ’Change the challenge’ section provided separately offers guidance for practitioners on how to differentiate the activity to meet the diverse needs of children in relation to Goodway et al. [1] notion of Space, Effort and Relationships (SER). This section was originally contained within the core activity cards, alongside the illustration of the activity and text supporting the establishment and playing of the game. Findings from the original feasibility trial [33] suggested the amount of detail on the card was overwhelming for some facilitators and feedback indicated that the ‘change the challenge’ section was not being used in the initial stages of delivery. Consequently, the authors decided to remove this aspect from the main activity card and present this information as a separate section within the resource as something that would be used following the initial establishment of the primary function of the game and assessment protocols. During the intervention, the facilitator modifies the activity using one or more of the SER principles to challenge the child in different ways within the general construct of the game. This allows for a movement focus to be maintained throughout the development of the game, whilst challenging children at different developmental levels to respond to the variation on the task created by SER.

Quick Response (QR) codes are used to support the ability of the facilitator to acquire the relevant information needed to establish the activity and assessment focus through viewing a video of (a) the activity being played (on the front of the card) and (b) the movement task being assessed (on the back of the card). This level of visual support has been recognised as an effective mode of information dissemination in previous developments of similar resources [34].

The integration of teaching and assessment guidance in a single resource is seldom seen in children’s physical education, physical activity or sport contexts. We have designed the resource in this way to encourage facilitators to view teaching, learning and assessment as interdependent aspects of a positive learning environment [35, 36]. Through the provision of activities with an associated assessment protocol it is also hypothesized that facilitators will use assessment data to inform subsequent curriculum design and tailor the choice of activities according to the developmental status of children within the group.

Illustrations used within the resource were designed with the following principles in mind: (i) characters to be gender and ethnicity neutral, (ii) text to be limited to minimal instructions, (iii) characters to be sufficiently human-like to identify changes in head, arms, body and legs to support facilitator recognition of movement changes (iv) use of colour and font-coding to identify which phase of development and movement category was being developed (v) navigation around the information on the card to be easily defined.

